## Abstract

**Background:**

Myopia prevalence has been increasing in the last decades, and its pathological consequences, including myopic maculopathy and high myopia-associated optic neuropathy, are now one of the most common causes of visual impairment. It is estimated that by 2050, more than 50% of Europeans and Americans will be myopes, which is alarming due to the high morbidity of myopes over − 6.00D. Once myopia has appeared, there are different options with scientific evidence to try to slow the axial length growth. Ophthalmic lenses are the less invasive treatment to control myopia, and there is evidence about the efficacy of different designs, mainly in the Asiatic population. However, new designs have been launched, and it is not known if efficacy is the same between Asiatic and European subjects. Thus, we have set up a randomized, controlled, double-blind, and multicenter trial to investigate the efficacy of a new design of ophthalmic lenses for myopia control in European children.

**Methods:**

A 2-year prospective, multicenter, randomized controlled, and double-blind clinical trial is used to investigate the efficacy of a new design of ophthalmic lenses to slow the progression of myopia. Three hundred children aged from 6 to 13 years old will be recruited and randomly assigned to a study or control group. The study group will be composed of 150 children wearing MyoCare while the control group will be composed of 150 children wearing Clearview. The inclusion criteria will be myopia with a spherical equivalent between − 0.75D and − 5.00D, astigmatism < 1.50D, and anisometropia < 1.00D and having a historical evolution of at least − 0.50 The primary outcome is to compare the mean annual progression of the spherical equivalent between both groups. The secondary outcomes are axial length, choroidal thickness, phorias, and accommodative status of both groups.

**Discussion:**

This study will be the first randomized and controlled clinical trial in European children with spectacle lenses based on simultaneous competing defocus. The results will shed light on the clinical evidence of spectacle lenses relying on this new design for the management of myopia with results of efficacy in the non-Asiatic population.

**Trial registration:**

EU Clinical Trials Register (EudraCT) 2022–001696. Registered on 27 April 2022. ClinicalTrials.gov NCT05919654. Registered on 26 June 2023.

## Introduction

### Background and rationale {6a}

The prevalence of myopia has been increasing in recent decades, and its pathological consequences, including myopic maculopathy and high myopia-associated optic neuropathy, are now one of the most common causes of visual impairment [1]. It is estimated that by 2050, more than 50% of Europeans and Americans and around 90% of the inhabitants of Southeast Asia will be myopic. This is alarming data due to the high morbidity of myopes who have more than − 6.00D [2].

Due to the previously exposed data, establishing strategies to prevent the onset of myopia and its progression in terms of the refraction (spherical equivalent refractive error in diopter (D) (SE) and the length of the eye (axial length in mm (mm) (AxL)) to high myopia (SE <  − 6D or > 26 mm) is highly recommended. Thus, an effective clinical intervention at an early age will reduce the further progression of myopia and inhibit the complications that are associated with myopia and especially high levels myopia, such as the said retinal pathologies [3].

There is already clinical and real-world evidence about effective actions and interventions to reduce the progression of myopia in terms of SE and AxL [4].

Once myopia has appeared, there are different techniques with clinical and scientific evidence to manage the progression of myopia (for both SE and AxL). Among the different techniques for the control of myopia, the following interventions are available [3, 5]:

Time spent outdoors: it is recommended that children spend between 80 and 120 min a day outdoors to reduce the progression and onset of myopia [6].Pharmacological options: The application of atropine at low concentrations (between 0.01 and 0.05%) has shown good results in slowing the progression of myopia [7, 8].Optical solution:Contact lenses:Dual focus and multifocal: these include a variety of contact lens designs that generally feature a central zone for distance vision and concentric rings or a positive power gradient design that increases toward the periphery of the lens [9–12].Orthokeratology (OK): the use of OK lenses, designed for night use to flatten the central cornea, causes an elevation of the corneal mid-periphery, which causes a peripheral myopic blurring that helps control the axial growth of the eye [13, 14].Ophthalmic lenses:Progressive and bifocal lenses: conflicting results and clinical evidence have especially been observed in the first year of such clinical trials [15–17].Peripheral defocus lenses: conflicting results and clinical evidence have especially been observed for a reduction of progression of the spherical equivalent refractive error [18–21].Simultaneous competing defocus: long-term clinical evidence with reductions of progression of both spherical equivalent refractive error and axial length [22, 23].

Of all the above-described options, ophthalmic lenses are the least invasive treatment to control myopia, so further research into new designs that improve current results should be a priority.

### Objective {7}

The objective is to set up a randomized, controlled, double-blind, and multicenter clinical trial to investigate the clinical evidence of a new design of ophthalmic lenses to reduce the progression of myopia.

### Trial design {8}

The trial design is a prospective, multicenter, randomized controlled, and double-blind clinical trial aimed to evaluate the efficacy of a new design of ophthalmic lenses to slow the progression of myopia in children.

## Methods: participants, interventions and outcomes

### Study setting {9}

The clinical trial is being done in the following ophthalmologic clinics in Spain and Portugal: Novovision (Madrid and Murcia, Spain), Virgen de Lujan clinic (Seville, Spain), Instituto clínico quirúrgico de Oftalmología—ICQO (Bilbao, Spain), Instituto de Microcirugía Ocular—IMO (Madrid, Spain), and Clínica Privada de Oftalmologia – CPO (Lisbon, Portugal). The trial is being coordinated by Universidad Complutense de Madrid and Instituto Superior de Educação e Ciências, ISEC Lisboa. Ethical approval was obtained from the Ethics Committee CEIm Hospital Clínico San Carlos. Written informed consent was collected from the parents/guardians and participants older than 12 years old before the enrolment. Table 1 shows the schedule of the different protocol phases: enrollment, follow-up visits, data collection, and assessment that were designed following the Standardized Protocol Items: Recommendations for Interventional Trials (SPIRIT) guidelines. The study flowchart is shown in Fig. 1.

**Table 1 Tab1:** Schedule of assessments and examination items

Date/item		Screening	Spectacles dispense	Follow-up					
		Day − 30 to day 0	V0	V1	V2	V3	V4	V5	V6
			Day 0	1 week ± 1 day	3 months ± 15 days	6 months ± 30 days	12 months ± 30 days	18 months ± 30 days	24 months ± 30 days
Informed consent signed		X							
Basic information	Demographics	X							
	History	X							
Refraction	Noncycloplegic autorefraction	X				X	X	X	X
	Subjective refraction	X				X	X	X	X
	Cycloplegic autorefraction	X				X	X	X	X
Visual acuity	Uncorrected visual acuity	X				X	X	X	X
	Best-corrected visual acuity	X				X	X	X	X
	Central visual acuity		X		X	X	X	X	X
	Peripheral visual acuity		X		X				
Eye examination	Keratometry	X				X	X	X	X
	Slit lamp examination	X				X	X	X	X
	Fundus examination	X							
	Intraocular pressure measurement	X							
	Axial length	X			X	X	X	X	X
	Choroidal thickness	X				X	X	X	X
Binocular vision	Accommodative LAG	X				X	X	X	X
	Monocular estimated method (MEM) retinoscopy	X				X	X	X	X
	Phoria (distance and near)	X				X	X	X	X
Spectacle fitting	Frame position and lens condition		X						
Questionnaires	Lifestyle	X							
	Spectacle lens performance and wearability		X	X	X

**Fig. 1 Fig1:**
[figure not shown]
Study flowchart

### Eligibility criteria {10}

The study group will be made up of children aged from 6 to 13 (at the time of inclusion in the study) with a historical annual progression of spherical equivalent refractive error of − 0.50D.

The following are the inclusion criteria:Age 6–13 yearsCaucasian ethnicityMonocular/binocular decimal visual acuity with correction ≥ 1.00Spherical equivalent between − 0.75D and − 5.00DAstigmatism≤ 1.50DAnisometropia ≤1.00DEvolution of at least − 0.50D in 1 year

The following are the exclusion criteria:Presence of ocular pathology or a history of ocular and systemic abnormalitiesStrabismus or binocular vision problemsHistory of eye surgeryHaving previously used some method to control myopiaHaving contraindications for the application of drugs for cycloplegia/corneal anesthesia

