### Outcomes {12}

#### Primary outcome

The primary outcome is to compare the mean annual progression of the spherical equivalent between myopic children treated with ZEISS MyoCare lenses and those who wear a conventional single-vision lens.

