### Sample size {14}

Based on an annual progression of − 0.50D, an estimated minimum efficacy of 50% compared to control, a power of 80%, an alpha of 5%, and a standard deviation for objective refraction of 0.70D, the size of the sample is 124.

Taking possible dropouts into account, 150 children will be included in the intervention group and 150 children in the control group.

Assignment to the different groups will be made by stratified randomization based on the age and spherical equivalent of the child. Randomization will be done automatically at the patient level by including the parameters of the initial visit in the eCRF. The researchers from the clinics will have partial access to the eCRF so that they will only be able to access the data that they have entered or must complete, not knowing the group assigned for each child.

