### Assignment of interventions: allocation

#### Sequence generation {16a}

The randomization has been programmed with minimization using 3 study variables for group stratification of sex, age group, and objective refraction group (spherical equivalent):Sex (2 options): male/femaleAge (2 options): 6–9 years/10–13 yearsSpherical equivalent (6 options): [− 0.5, − 1.25], [− 1.25, − 2], [− 2, − 2.75], [− 2.75, − 3.5], [− 3.5, − 4.25], [− 4.25, − 5]

The values will be computer-generated and assigned to the patients as A for the control group and B for the study lenses, with a 1:1 ratio.

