#### Implementation {16c}

All the children will pass the screening visit to assure that they comply with the inclusion criteria. Once the eCRF for the screening visit was filled in fully, the researcher from the clinic will use the specific option of the eCRF to generate the allocation sequence number. The children will be automatically assigned to the control or intervention group, but only the principal investigator could access this information.

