### Statistical methods for primary and secondary outcomes {20a}

The statistical analysis of this study will be made by a statistician who will participate in the entire process of study design, implementation, data management, analysis of study results, and summary. Once the study protocol and CRF are completed, the statistical analysis plan will be finalized before the study data is locked to complete the statistical analysis report.

Statistical analysis will be performed using Stata. The statistical description and inference of the data will be based on the characteristics of the data and the selection of applicable descriptive indicators and hypothesis testing methods.

Efficacy analyses will be performed based on the full analysis set and per the protocol set. All baseline demographic analyses will be performed based on the analysis set.

The data included will be analyzed using the applicable statistical methods according to their distribution characteristics. Unless otherwise specified, quantitative endpoints will be described by calculating the mean, standard deviation, median, minimum, maximum, lower quartile (Q1), and upper quartile (Q3), and the categorical assessments will be described by calculating the number and percentage of subjects. Quantitative endpoint cluster comparisons will be performed using the cluster *t*-test, or Wilcoxon rank sum test depending on the data distribution, and categorical endpoint cluster comparisons will be performed using the chi test—square or the exact probability test.

For studies of the evolution of the progression of myopia, ANOVAs of repeated measures or Kruskal–Wallis tests will be performed.

Finally, to study how the age and graduation of the child at the start of treatment are affected, a linear regression model will be built to assess the annual change in myopia and axial length analyzing data from the right eyes of all children, what is a standard practice in this kind of studies [29–32].

All statistical tests will be determined to be statistically significant based on *P* < 0.05.

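### Prior-year SE progression must be established for eligibility, but the planned between-arm test is unadjusted, so any outcome variance it explains is left in the error term

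*Protocol article*

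**What the plan says.** Eligibility criteria {10} describes children "with a historical annual progression of spherical equivalent refractive error of" −0.50 D, and the list of inclusion criteria makes this a minimum over 1 year. Implementation {16c} places the check before allocation: "All the children will pass the screening visit to assure that they comply with the inclusion criteria". Table 1 shows an item called History at screening but no entry for an earlier refraction or a progression rate.

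The primary outcome is to "compare the mean annual progression of the spherical equivalent between myopic children treated with ZEISS MyoCare lenses" and those wearing single-vision lenses.

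Allocation under Sequence generation {16a} uses "minimization using 3 study variables for group stratification of sex, age group, and objective refraction group (spherical equivalent"). Sample size {14} describes "stratified randomization based on the age and spherical equivalent of the child". Prior progression is in neither.

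Statistical methods {20a} states the between-arm test: "Quantitative endpoint cluster comparisons will be performed using the cluster" t-test, or a Wilcoxon rank sum test, depending on the distribution. Since Sample size {14} randomises individual children, I read cluster here as group. Changes over time are to be studied by repeated-measures ANOVA or Kruskal–Wallis. For the effect of starting age and refraction, "a linear regression model will be built to assess the annual change in myopia and axial length". Prior progression is not named in any of these.

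**The concern.** A child's recent rate of progression is a likely predictor of the next year's rate. The design suggests as much: it selects on prior progression, and the sample size assumes an annual progression of −0.50 D, the same figure as the entry threshold. The criterion is only a floor, so children just at 0.50 D enter together with children progressing much faster. Two children of the same sex, age group and refraction class can also differ in recent rate, so the minimisation factors do not fully stand in for it.

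An unadjusted test leaves the spread between fast and slow progressors in the residual. The confidence interval for the lens effect is then wider than it would be with adjustment. A chance difference between arms in prior rate also shifts the estimate, in proportion to the correlation.

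**Working it through.** **Inputs from Sample size {14}:** control progression 0.50 D per year; 50% efficacy, so the difference is 0.50 × 0.50 = 0.25 D; SD 0.70 D; alpha 5%; power 80%; stated size 124; 150 enrolled per arm.

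**The plan's own figure.** Two-sided, normal approximation: n per arm = 2 × (1.960 + 0.842)² × 0.70² / 0.25² ≈ 123.1, rounded up to 124. The t-distribution gives 124.04. A one-sided test would give 97. The stated 124 is therefore a two-sided, per-arm figure computed on the unadjusted SD. Unadjusted power is 80.3% at 124 per arm and 87.1% at 150 per arm. The allowance for dropout is (150 − 124)/150 = 17.3%.

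**Effect of adjustment.** Let r be the correlation between prior-year and on-study annual SE change. The documents give no value, so r is an assumption, shown over a range. Residual SD = 0.70 × √(1 − r²).

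| r | variance removed (r²) | residual SD (D) | n per arm for 80% | power at 124 per arm | power at 150 per arm |
|---|---|---|---|---|---|
| 0 | 0% | 0.700 | 124 | 80.3% | 87.1% |
| 0.1 | 1% | 0.696 | 122 | 80.7% | 87.5% |
| 0.2 | 4% | 0.686 | 119 | 81.9% | 88.4% |
| 0.3 | 9% | 0.668 | 112 | 83.8% | 90.0% |
| 0.4 | 16% | 0.642 | 104 | 86.6% | 92.1% |

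At 124 per arm the t-distribution gives 80.0%, 81.6%, 83.6% and 86.4% for r = 0, 0.2, 0.3 and 0.4, the same within rounding of method.

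**Chance imbalance.** The standard error of the difference is 0.70 × √(2/124) = 0.089 D. If the arms differ in prior rate by 1.96 of its own standard errors, the unadjusted estimate is expected to move by 1.96 × r × 0.089 D. That is about 0.017, 0.035, 0.052 and 0.070 D for r = 0.1, 0.2, 0.3 and 0.4, or 7%, 14%, 21% and 28% of 0.25 D.

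**What lowers r or the gain**

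- *Entry floor.* Truncating a normal prior rate at its median shrinks its SD to √(1 − 2/π) = 0.603 of the original. With u = 0.603, the restricted correlation is r·u/√(1 − r² + r²u²). A population r of 0.3, 0.5 or 0.6 becomes 0.19, 0.33 or 0.41. The position of the floor is also an assumption.
- *Partial correlation.* If r is taken beyond age and baseline SE, which explain a share R² of the outcome variance, prior rate removes r² × (1 − R²) of the 0.49 D² total. The table is then an upper bound on what prior rate adds.
- *Shared reading.* If the prior change ends at the screening refraction, and the on-study change starts there, error in that reading enters the two changes with opposite signs and pulls a positive r towards zero.
- *Noisy history.* Recruitment {15} draws on clinic patients and school screenings, and the article does not say how or over exactly what interval the earlier refractions were taken.

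**The case against.** The strongest reply is that covariate choice belongs in the statistical analysis plan, which {20a} says will be finalised before lock. The article's statement that no additional analyses are planned sits under a subgroup heading and does not forbid adjustment. That is fair as far as it goes, and I place no weight on that statement. But {20a} is not silent: it names an unadjusted test for quantitative endpoints, and the point is that a better method than the stated one is available.

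A second reply is that the criterion needs only a threshold to be met. This stands. A reader might infer that every child's numeric rate is already in the database. The article shows only that compliance is checked, and Table 1 lists only History, so the eCRF may hold a yes/no.

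Third, prior change is not strictly the same measurement as the outcome. On-study refraction follows a protocol (cycloplegic, mean of 3 readings); the earlier refractions may not have. This too stands, and it lowers the likely gain.

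Fourth, chance imbalance in any prognostic variable is already covered by the error rate of an unadjusted test. That is correct over repeated trials. What remains is that, for the allocation actually obtained, adjustment would remove the part of the shift that prior rate explains.

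**Conclusion.** The point holds as a missed gain in precision and in protection against chance imbalance. At an assumed r of 0.1 to 0.4, power at 124 per arm would rise from about 80% to about 81–87%. At r of 0.1 to 0.2 the gain is under 2 percentage points, and given the entry floor, noisy histories and the shared screening reading, the true value could lie there.

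Two stronger readings are not supported. One is that the lens effect will be biased: allocation is randomised, so omitting a baseline predictor produces no systematic error. The other is that the sample size is wrong: 124 per arm was computed on the unadjusted SD and reproduces exactly for the test the article names.

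**What to change.** In Statistical methods {20a}, make the between-arm comparison of annual SE progression a linear model with arm, the minimisation factors (sex, age, baseline SE) and the recorded prior-year SE change (continuous, D per year) as baseline covariates. Use the same model form for axial length. Fill a missing prior value with the overall mean across both arms, so that no child drops out of the intention-to-treat analysis. Fix this before lock.

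Where the eCRF holds only a yes/no, the value should be transcribed from source records that predate allocation. Enrolment has ended (Trial status), so this would happen after allocation, and the principal investigator and coordinating team can see the assignments ({17a}). Staff blinded to allocation should therefore do it.

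Leave the regression on starting age and refraction as it is. It serves a separate secondary objective, and conditioning on prior progression would change what its coefficients mean. Minimisation itself can no longer be changed.

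The cost is extra model terms in the analysis plan and some transcription work, for a gain that may be small. No new visit or measurement is needed.

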### Who will take informed consent? {26a}

Written informed consent was collected from the parents/guardians in the clinics before the screening visit. Participants older than 12 years old will sign also the informed consent adapted to their educational level.

### Additional consent provisions for collection and use of participant data and biological specimens {26b}

N/A.

### Interventions

#### Explanation for the choice of comparators {6b}

Optical design solutions such as dual focus/multifocal contact lenses and OK lenses based on the concept of simultaneous competing defocus have scientific evidence to reduce the progression of myopia in terms of SE and AxL [11, 13, 14, 24, 25]. This evidence-based knowledge from scientific concepts was translated into the lens design of ophthalmic lenses by taking into consideration the roughing eye. Applying simultaneous competing defocus due to cylindrical annular refractive elements, the eye experiences conflicting visual signals between the fovea and the periphery [23, 26]. These elements adopt optical microstructures with alternating defocus and correction zones, correcting myopia along the visual axis and simultaneously imposing relative myopic defocus over a large part of the retina for myopia progression management. Additionally, the back surface of the lenses is further supported by freeform optimization to correct the eye’s refractive error for all viewing angles and to minimize unintended hyperopic defocus for oblique views through the lens periphery.

#### Intervention description {11a}

Children assigned to the study group will wear ZEISS MyoCare lenses, while those assigned to the control group will wear conventional ZEISS ClearView single-vision lenses in their spectacles. Both lenses will be made of the same material (MR8) and hard as well as anti-reflection coating (ZEISS DuraVision Platinum) and will have the same surface treatments.

The following is the general overview:Subjective refraction (endpoint: best visual acuity with the most positive sphere).Objective refraction after cycloplegia (mean of 3 measurements).Ocular biometry (five measurements using IOLMaster 700 (Carl Zeiss Meditec AG, Jena, Germany)).OCT: spectral domain OCT using volume scan (and enhanced depth imaging) to visualize the choroid (ZEISS CIRRUS 5000, Carl Zeiss Meditec AG, Jena, Germany or Spectralis de Heildebergd Engineering) for 6 × 6 mm^2^ area. The choroidal thickness will be evaluated by automatic segmentation.Slit lamp examination.Intraocular pressure.Fundus check.Parameters of wear.Monocular measurement of distance and near visual acuity.Peripheral visual acuity.Distance phoria, near phoria @ 33 cm, and accommodative lag @ 33 cm.Vision quality, visual comfort, quality of life, and frequency of visual symptoms with lens wear are to be graded by the subjects themselves through questionnaires.

Table 1 describes the different measurements taken in each of the visits.

